**Introduction**

Hypertension is a common disease among population especially in the elderly and is a major risk factor for developing cerebrovascular and cardiovascular disease. Prevalence of hypertension in Thailand has been increasing over time; about 24.7% of population was diagnosed with hypertension in 2013. Major problems are unawareness and uncontrolled blood pressure^(1)^. Despite pharmacological management, one of the best-proven non-pharmacological interventions for prevention and treatment of hypertension is physical activity or exercise^(2)^. The 90-150 minutes per week of moderate intensity aerobic exercise has been long known and often prescribed to patients^(2)^. However, aerobic exercise usually gains more popularity and adherence from young adult group rather than elderly group. The barriers to aerobic exercise training are mindset among many elderly that exercise is only for young adult, and multiple comorbidities in which the most common are arthritis and other musculoskeletal disorder, that interfere with walking and related activities^(3)^. It is often too hard and too difficult for most of the elderly hypertensive patients to perform aerobic exercise due to declined overall activity performance and frailty. There was a survey in 2015, reveals that among overall sedentary Thai population, about 43.6% are aged more than 50 years old. While among Thai population who have adequate physical activity, the elderly are counted for only 33.8%^(4)^. The challenge for clinicians is to convince the elderly, who usually have not been exercise for many decades, to start engaging in suitable physical activities and exercise for their age and physical function.

In recent years, isometric resistive exercise is known to be an alternative exercise to reduce blood pressure. Several randomized-controlled trials (RCT) have proven the effectiveness of this kind of exercise, systematic reviews and meta-analysis were also conducted and confirmed that isometric resistive exercise produces a significant anti-hypertensive effect in young normotensive adults, older pre-hypertensive, and older medicated hypertensive patients ^(5-13)^. The most common isometric resistive exercise training among several studies is isometric handgrip exercise. The training protocol usually use the 30% maximum voluntary contraction (MCV) as the intervention group and 5% MCV or sedentary as the control group, performing four set of 2 minutes isometric contraction with a brief rest, conducting period from 4-20 weeks^(5-7, 14)^.

A 2017 ACC/AHA Guideline for the Prevention, Detection, Evaluation, and Management of High Blood Pressure in Adults recommends 4 sets of 2-minutes of 30-40% maximum voluntary handgrip contraction with 1 minute resting between exercises, 3 sessions per week for 8-10 weeks, approximately reduces systolic blood pressure reduction by 5mmHg in hypertensive and 4mmHg in normotensive patients^(2)^.

Mechanism for explaining blood pressure reduction remains unclear, but several hypotheses are proposed. A reactive hyperemia due to isometric resistive exercise contributes to the increased basal production of nitric oxide that improved resistance vessel endothelial function^(9)^. The improved systemic endothelial function may leads to a reduction in systemic total peripheral resistance^(8)^. Other possible mechanisms include the autonomic modulation by decreased sympathetic, and enhanced parasympathetic modulation of both heart rate and blood pressure ^(9, 10)^, the increased training limb artery diameter, blood velocity, and blood flow in concert with reduced vascular conductance and enhanced endothelial-dependent vasodilatation^(11)^.

Although isometric handgrip exercise has been previously feared for increasing blood pressure during the resistive phase, many studies are conducted and proved that it is a safe, well-tolerated procedure and cause no adverse effects that induce harmful hemodynamic responses^(15, 16)^. A study in 2011 by Araújo et al investigated the acute response during acute isometric handgrip exercise in elderly populations. There was an increase in SBP, DBP and HR by 16mmHg, 7 mmHg and 3 bpm respectively^(16)^, and these effect had returned to baseline after 1 minute of post-exercise recovery. There was also a study conducting submaximal isometric handgrip training in active cardiopulmonary rehabilitation patients and reported to be well tolerated and requiring minimal exertion.^(17)^ Another worrisome effect is the post-exercise hypotension (PEH) that was commonly reported in aerobic exercise, a study in 2013 by Olher et al conducted in hypertensive elderly women reported that was no post-exercise hypotension or cardiovascular overload occurred in the isometric handgrip exercise.^(15)^

Despite promising evidences of isometric handgrip exercise on blood pressure reduction, most of the trials are hospital-based or lab-based training protocols under direct supervision using expensive dynamometer (20,000 THB) as exercise equipment.

In order to make isometric handgrip exercise becomes more practical and accessible, so that general population, especially in elderly patients who cannot tolerate or unable to perform standard aerobic exercise due to many difficulty and frailty, would gain benefits from practicing this at home without having to travel to lab or hospital to do the isometric handgrip exercise. Since isometric handgrip exercise is easy to perform, short duration of training, and could be perform along with their leisure activities and transportation. We want to test whether isometric resistive exercise is an effective home-based practical procedure. The aim of this study is to access the effectiveness of home-based isometric handgrip exercise using inexpensive commercial available device in reducing resting SBP in hypertensive elderly patients. We also would like to access the changes in resting DBP, HR and handgrip strength after being trained, together with the satisfaction and any possible musculoskeletal side effect of this exercise.

**Literature review**

In 2014, an anchor systematic review and meta-analysis by Debra J. Carlson et al has revealed the effectiveness of isometric resistance training lasting 4 or more weeks in lowering systolic blood pressure (SBP) by -6.77mmHg(95%CI -7.93,-5.62;P<0.001), diastolic blood pressure (DBP) by -3.96mmHg(95%CI -4.80,-3.12;P<0.001), and mean arterial pressure (MAP) by -3.94mmHg(95%CI -4.73,-3.16;P<0.001), respectively^(5)^. Another systematic review and meta-analysis in 2015 by Jodie D Inder et al reported a subgroup analysis that anti-hypertensive effects is larger in hypertensive male aged ≥45years, using unilateral arm isometric resistive training conducting for at least 8 weeks^(6)^. These two systematic reviews, which were cited in 2017 AHA’s hypertension guideline, retrieved data from common RCTs regarding isometric resistance exercise with different characteristics: unilateral/bilateral/alternating isometric handgrip contraction, double leg extension exercise.

In 2018, K.F. Goessler et al conducted a home-based randomized controlled trial using telemonitoring and telecoaching to compare BP response in isometric handgrip exercise versus moderate intensity aerobic exercise in healthy adults. Trial was 8 weeks duration with handgrip group performing daily, while aerobic group performing moderate intensity aerobic exercise for at least 150 minutes per week. The result showed a significant reduction in both ambulatory and office DBP in aerobic group, but significant reduction in only office SBP in handgrip group. They concluded that aerobic exercise should remain a number one recommendation in the prevention and treatment of hypertension, while isometric handgrip exercise could be a useful tool for lowing blood pressure in elderly adult or patients who have multiple comorbidities.^(18)^

There was a RCT in 2002 conducting an isometric handgrip exercise in hypertensive elderly population, aging 60-80 years old, and revealed significant hypotensive effect following 10 weeks of standard 4sets of 2minutes handgrip exercise at 30% MVC, 3 days per week. SBP was reduced from 156±9.4 to 137±7.8 mmHg in exercise group versus 152±7.8 to 144±11.8 mmHg in non-exercise group. 75% of the hypertensive elderly participants had been taking antihypertensive medication for many years.^(10)^

There was a RCT in 2008 using an inexpensive spring handgrip-training device with intensity about 30-40% MCV in normotensive patients, also demonstrated a significant reduction in resting SBP and DBP, 10±3 mm Hg and 3±1 mm Hg respectively. The study design was 3 sessions/week, training in lab-based 2 sessions/week and home-based 1 session/week, and was carried on for 8 weeks. They used 3 different intensity handgrip spring device based on each MVC. The control group was arranged for discussion session about hypertension once a week. ^(13)^

**Study design**

This is a randomized-controlled single blinded trial. The assessors are blinded from knowing which group participants are assigned. Eligible participants are randomized into either intervention group or control group using blocked randomization.

**Method**

This study will be conducted after being approved by the Institutional Review Board of the Faculty of Medicine, Chulalongkorn University, Bangkok, Thailand.

**Participants**

Participants are recruited from Comprehensive Geriatric Clinic in King Chulalongkorn Memorial Hospital, Bangkok, Thailand. The doctor and nurse in clinic are contacted and informed by researchers about this project and refer eligible population to meet researcher. Referring physician will be masked from knowing if the patients decide to join the study or not.

**Inclusion criteria.**

1. Elderly adults, aged 60 years or more.
2. Diagnosed and being treated for hypertension, whether receiving pharmacotherapy or not.
3. Maximum grip strength ranging from 10-40kg.
4. Willing to join the study.

**Exclusion criteria.**

1. Resting SBP≥160 or DBP≥100^(19)^.
2. Contraindicated for resistance exercise^(20)^:
   - Recent myocardial infarction / CABG within 12weeks
   - Arrhythmia
   - Acute congestive heart failure
   - Unstable angina
   - Severe joint or muscle pain during unresisted movement
   - Inflammatory neuromuscular disease
3. Musculoskeletal problems preventing handgrip exercise such as

- Trigger finger

- Carpal tunnel syndrome

- De Quervain’s tenosynovitis

- Rheumatoid arthritis

- Osteoarthritis of hand

**Dropout criteria** Patients with one or more of the following conditions are classified as dropout

- Antihypertensive medication adjustment within study period.
- Physical activity or exercise adjustment within study period.
- Patients who have complication regarding handgrip exercise.

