**Control group**

Participants are asked to do non-resistive hand exercise with the chosen hand by simply grasp without squeezing, in total of 4 sets of 2-minutes grabbing with 1 minute resting between exercises.

After completing the study, the spring handgrip device with corresponding resistance level will be given to each participants in control group, also with exercise training session from researcher.

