**Sample size calculation**

A sample size of 36 participants (18 patients per group) is calculated based on mean difference and SD from Millar PJ et al. study in 2008^(13)^ with 5% error and 90% power.

Formular n/group = 2(Zα/2 + Zβ)2 σ2 / (X1-X2)2

where σ2 = [(n1-1) S12+(n2-1)S22] / (n1+ n2 - 2)]

X1-X2 = (-10) – (-1) = 9, SD1 = 8.98, SD2 = 2.36, n1 = 24, n2 = 25

α = 0.05, β = 0.10, Zα/2 = 1.96. Zβ = 0.84

n/group ~ 12

Since home-based protocol is susceptible to higher dropout rate, we estimate 30% of dropout rate and calculate total n/group = 18

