**Statistical analysis**

Statistical analyses are performed using SPSS Statistics Version 22. Demographic data are analyzed and present as mean, SD and percent. Within group comparison is used to analyze pre-post treatment using paired T-test. Between-group comparison is used to analyze mean difference between group using unpaired T-test if baseline characteristics are similar, or ANCOVA if baseline characteristics are different. All statistical tests are two-tailed, statistical significance is set at p<0.05, and using intention to treat analysis.

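### The dropout criteria sit uneasily with the stated intention-to-treat analysis: if participants so labelled leave the comparison, the SBP difference can be biased in either direction

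*Protocol*

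**What the plan says.** The Exclusion criteria section ends with a list of dropout criteria: "Patients with one or more of the following conditions are classified as dropout". The three conditions are "Antihypertensive medication adjustment within study period", "Physical activity or exercise adjustment within study period" and "Patients who have complication regarding handgrip exercise". This is the only definition of dropout that the protocol gives.

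Four other places bear on it:

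- **Statistical analysis** fixes the analysis principle: "All statistical tests are two-tailed, statistical significance is set at p<0.05, and using intention to treat analysis".
- **Sample size calculation** arrives at about 12 per group and then adds an allowance: "we estimate 30% of dropout rate and calculate total n/group = 18".
- **Outcome measurement** appoints all participants at the clinic after 8 weeks. It does not say whether this includes those already classified as dropouts.
- **Both groups** schedules a telephone call every 2 weeks, which checks for these same events.

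**The concern.** A participant whose tablets are changed, who takes up other exercise or who gets a sore hand can still attend at week 8 and have blood pressure measured. The dropout label is therefore not a description of missing data. It is triggered by events after randomisation, and two of the three have an evident link to the outcome or the arm:

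- Antihypertensive treatment is changed in response to blood pressure, which is the outcome.
- Handgrip complications are expected mainly in the resistive arm, because of the control task: "Participants are asked to do non-resistive hand exercise with the chosen hand by simply grasp without squeezing".
- Activity changes could also differ by arm, since only the assessors are blinded. The protocol gives nothing by which to judge how likely that is.

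If these participants are left out, the groups compared are no longer the groups randomised. Losing controls whose SBP rose hides a real benefit. Losing intervention participants who did badly creates an apparent one.

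Conduct is at stake as well as analysis. If site staff take the label to mean that follow-up ends, the week-8 reading is never taken and no later analysis plan can recover it. Participants with complications would also be missing from the week-8 questionnaire on musculoskeletal side effects.

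**Working it through.** **1. The plan's own figure.** The inputs are from Sample size calculation: difference 9 mmHg, SDs 8.98 and 2.36, n 24 and 25.

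- Pooled variance = (23 × 8.98² + 24 × 2.36²)/47 = 42.31, so SD = 6.50.
- n per group at 90% power = 2 × (1.96 + 1.28)² × 42.31/9² = 10.97, or 11. At 12 per group the noncentral t gives 89.9% power, so the stated 12 is consistent with 90%.
- The printed Zβ of 0.84 would give 2 × (1.96 + 0.84)² × 42.31/81 = 8.19, or 9. That is a separate matter and does not affect this point.
- Dropout allowance: 12/(1 − 0.30) = 17.1, rounded up to 18. The stated 18 reproduces.

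The design thus counts on 12 per group contributing to the comparison.

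**2. The passages side by side.** The dropout definition rests on events, not on a missing measurement. The allowance treats dropouts as not contributing. The analysis statement requires every randomised participant in the assigned arm. The three fit together only if dropouts under the definition are still measured and analysed, which the protocol does not say.

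**3. Worst-case shift.** Suppose the k largest SBP changes are lost from one arm of 18 and nobody from the other. The arm mean moves by SD × (sum of the k largest expected normal order statistics)/(18 − k). For n = 18 the three largest are 1.820, 1.350 and 1.066.

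| k lost | Multiplier | SD 6.5 | SD 9.6 |
|---|---|---|---|
| 2 | 3.170/16 = 0.198 | 1.3 mmHg | 1.9 mmHg |
| 3 | 4.236/15 = 0.282 | 1.8 mmHg | 2.7 mmHg |

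The SD of 9.6 is an assumption. It takes the ± values for the 2002 trial in the Literature review (9.4 and 7.8; 7.8 and 11.8) as SDs, with a pre-post correlation of 0.5:

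- √(9.4² + 7.8² − 9.4 × 7.8) = 8.7
- √(7.8² + 11.8² − 7.8 × 11.8) = 10.4
- pooled: √((75.88 + 108.04)/2) = 9.6

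Against the planned 9 mmHg, the shifts are 14% to 20% at SD 6.5 and 21% to 30% at SD 9.6. The sign depends on which arm loses participants.

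**4. Milder selection.** Normal SBP changes were simulated at SD 6.50, with a control mean of −1. The dropout mechanisms are assumed.

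| True difference | Who is dropped | Estimate in those kept |
|---|---|---|
| −9 | change above +5, probability 0.5 to 1.0, both arms | −8.2 to −7.1 |
| −5 | same rule | −4.4 to −3.6 |
| 0 | same rule | 0 |
| 0 | 10% to 30% of the intervention arm only, three times as likely in the half with the less favourable change | −0.3 to −1.1 |

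In the first row the rule removes 0.5% to 1.1% of the intervention arm and 9% to 18% of controls.

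**5. Effect of keeping everyone.** On the plan's inputs, noncentral-t power is 98.1% with 18 per group analysed, against 89.9% with 12. This assumes that the full 9 mmHg also holds in those who would otherwise be dropped.

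**The case against.** The strongest reply is that the text can be read consistently. No sentence says that dropouts' data are discarded or that their week-8 visit is cancelled. All participants are appointed at week 8, and the analysis is declared to be "using intention to treat analysis". The events may simply be labels, with the participants still measured and analysed as allocated, and an analysis plan not shown here may say so.

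A reader might infer from 12 becoming 18 that a completers-only analysis is planned. The documents do not support that. An allowance for lost data is compatible with intention to treat, and the reason given is that home-based protocols lose more participants. Nor does the protocol say that the 30% consists of these three conditions, so it is not a measure of how many participants they affect.

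A reader might also infer that the comparison is biased in a known direction. That does not follow either. Medication-driven loss under the same SBP rule in both arms gives no bias when there is no true effect, and shrinks a real one. A false benefit needs losses that differ by arm. The Participants section masks the referring physician to whether the patient joined, which limits prescribing changes driven by the arm. The protocol gives no complication rate and describes the exercise as well tolerated.

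These limits stand. What remains is that the only dropout definition given is by events after randomisation, and nothing ties it to the week-8 visit or to the intention-to-treat statement.

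**Conclusion.** The point holds in conditional form. The dropout criteria, the sample-size allowance and the analysis principle are not reconciled. If dropout is applied in its usual sense, the primary comparison is not by intention to treat, and the SBP difference can be biased in either direction.

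The size cannot be fixed from the document. The shifts of 1.3 to 1.8 mmHg (SD 6.5) and 1.9 to 2.7 mmHg (SD 9.6, resting on an assumed correlation) are one-sided worst cases, not forecasts. For a given SD and number lost from one arm, weaker selection gives smaller shifts. This is more than a detail for the analysis plan, because the label can decide whether the week-8 reading is taken at all.

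**What to change.** Reconcile the dropout criteria, Sample size calculation and Statistical analysis as follows:

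- Rename the three conditions as events to be recorded during follow-up.
- Reserve the word dropout for participants with no week-8 measurement, so that the 30% allowance covers only true loss of week-8 data.
- State that every randomised participant is measured at the scheduled week-8 visit, whether or not the exercise is continued.
- Make the primary analysis all randomised participants in their assigned arm.
- Report the set without these events as a labelled per-protocol sensitivity analysis.

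None of this alters clinical management. N stays at 36, and the cost is protocol wording plus an already scheduled visit for a few participants. The downside is that medication changes may dilute the estimate; the sensitivity analysis gives a view of this, subject to the selection described above.

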**Procedure**

Patients are screened for eligibility and provided information about this study by researcher. They are free to make decision in participating the study. The willing patients then signed an informed consent for participation. They are asked to choose their preferred hand for training and use that side for training and measurement.

**Isometric Handgrip Exercise intervention group**

We have reviewed the commonly used protocol in previous studies and 2017 AHA’s hypertension guideline; intensity in the intervention group is usually 30%-50%MVC. Since there is no commercially available spring handgrip device that can precisely adjust resistance load to the desirable value, we make an adaptation to protocol to make it more simple and suitable for home-based exercise. We classify participants into 2 intensity levels: 5kg and 10kg resistance load, based on commercially available device.

All participants are asked to complete 3 maximum voluntary contractions (MVC) in preferred hand using Jamar plus+ digital hand dynamometer to determine their average MVC. Participants in the intervention group with MVC range from 10-19.9kg or 20-40kg are provided a 5kg or 10 kg resistance load handgrip device respectively, which approximated their 25%-50% MVC. They use the provided handgrip device to complete 4 sets of 2-minutes handgrip contraction with 1 minute resting between exercises, with chosen hand.

**Control group**

Participants are asked to do non-resistive hand exercise with the chosen hand by simply grasp without squeezing, in total of 4 sets of 2-minutes grabbing with 1 minute resting between exercises.

After completing the study, the spring handgrip device with corresponding resistance level will be given to each participants in control group, also with exercise training session from researcher.

**Both groups**

First exercise session is conducted under supervision by a researcher. The immediate hemodynamic effect of exercise is obtained during this session to ensure that the increased blood pressure during resistive exercise is within safety limit of SBP≤220 and DBP≤105^(19)^. All participants are required to familiarize themselves with their study protocol before leaving their first visit at clinic and exercise diary is given.

During 8 weeks of study, both groups are committed to perform their procedure 3 days per week and record their activity in exercise diaries that were given. A telephone visit by research member is scheduled every 2 weeks to surveillance for adherence to the study protocol, complication and to ensure no changes in antihypertensive medications or exercise.

**Outcome measurement**

Baseline blood pressure, grip strength and skeleton muscle mass (SMM) are measured at the first visit. After 8 weeks, all participants are appointed at clinic to assess blood pressure, grip strength and SMM. We use InBody 770 body composition and body water analyzer to measure SMM. Thai short IPAQ is used to assess the physical activity level at both visits^(21)^. Questionnaire is given concerning the satisfaction of this exercise and any possible post-procedural musculoskeletal side effect. Blood pressure, grip strength and SMM are measured by the same research member who is blinded to randomization and treatment procedure.

